## Abstract

**Background:**

Low-level laser therapy (LLLT) has been widely used as adjuvant strategy for treatment of musculoskeletal disorders. The light-tissue interaction (photobiostimulation) promotes analgesic and anti-inflammatory effects and improves tissue healing, which could justify the recommendation of this therapy for patients with fibromyalgia, leading to an improvement in pain and possibly minimizing social impact related to this disease. The present study proposes to evaluate the effect of LLLT on tender points in patients with fibromyalgia, correlating this outcome with quality of life and sleep.

**Methods/design:**

One hundred and twenty patients with fibromyalgia will be treated at the Integrated Health Center and the Sleep Laboratory of the Post Graduate Program in Rehabilitation Sciences of the Nove de Julho University located in the city of Sao Paulo, Brazil. After fulfilling the eligibility criteria, a clinical evaluation and assessments of pain and sleep quality will be carried out and self-administered quality of life questionnaires will be applied. The 120 volunteers will be randomly allocated to an intervention group (LLLT, n = 60) or control group (CLLLT, n = 60). Patients from both groups will be treated three times per week for four weeks, totaling twelve sessions. However, only the LLLT group will receive an energy dose of 6 J per tender point. A standardized 50-minute exercise program will be performed after the laser application. The patients will be evaluated regarding the primary outcome (pain) using the following instruments: visual analog scale, McGill Pain Questionnaire and pressure algometry. The secondary outcome (quality of life and sleep) will be assessed with the following instruments: Medical Outcomes Study 36-item Short-Form Health Survey, Fibromyalgia Impact Questionnaire, Berlin Questionnaire, Epworth Sleepiness Scale and polysomnography. ANOVA test with repeated measurements for the time factor will be performed to test between-groups differences (followed by the Tukey-Kramer post hoc test), and a paired *t* test will be performed to test within-group differences. The level of significance for the statistical analysis will be set at 5% (*P* ≤0.05).

**Trial registration:**

The protocol for this study is registered with the Brazilian Registry of Clinical Trials – ReBEC (RBR-42gkzt)

## Background

According to the American College of Rheumatology (ACR), fibromyalgia is a chronic musculoskeletal condition characterized by generalized pain for at least three months in combination with sensitivity in 11 or more of the 18 points sensitive to palpation in different parts of the body, known as tender points [1,2]. Fibromyalgia was not a clinically well-defined condition before the 1970s, and unlike what was thought in the past, this is not an inflammatory condition and does not lead to joint impairment or deformities. However, the chronic nature of this condition has a negative impact on quality of life [3].

The most widely accepted theory is that fibromyalgia is caused by an abnormality in pain modulation mechanisms - a central nervous system disorder in regulating sensitivity to pain. Thus, an individual may exhibit a reduction in serotonin (neurotransmitter of the inhibitory descending system) and in increase substance P (neuroexcitatory substance involved in the conduction of pain) in the central nervous system [4].

Fibromyalgia is often associated with other syndromes, such as fatigue, sleep disorders, morning stiffness and psychological disorders, such as anxiety and depression. Sleep disorders are closely linked to somatic symptoms in patients with fibromyalgia and not to their personality. The most common complaints are difficulty falling asleep, frequent awakening during the night, difficulty getting back to sleep, restless superficial sleep and early rising, the consequences of which are nonrestorative sleep and a sensation of weariness, which contribute toward a poor quality of life. Thus, non-restorative sleep is an important aspect among the manifestations of fibromyalgia, which makes the investigation into primary sleep disorders essential to the assessment of affected individuals [5,6]. The complexity of the factors involved regarding both diagnosis and adequate treatment underscores the need for further studies aimed at broadening knowledge on the effects of this condition on patients.

There are several treatment options for fibromyalgia, such as drugs [7,8], psychotherapy [9], hydrotherapy [10], electrotherapy [11], exercise [12] and laser therapy [13,14]. However, there is no consensus or defined protocol regarding the use of these treatment options. Low-level laser therapy (LLLT) is one of the more recent pain treatment modalities in the field of physical therapy. According to Laakso *et al*. [15], the analgesic effect of phototherapy may be mediated by hormonal/opioid mechanisms, the responses of which depend directly on the dose and wavelength used to irradiate the tissue. Thus, the parameters directly affect the results. LLLT is also reported to act on peripheral neural stimulation and the regulation of microcirculation, interrupting pain mechanisms and promoting analgesia [16]. The normalization of microcirculation and the capacity of neural transmission obtained through laser therapy have been described as responsible for the interruption of the vicious circle that gives rises to and perpetuates pain [13].

In last ten years, important advances have occurred in the therapeutic use of photobiostimulation with low-level lasers. Such advances have occurred due to a greater understanding of the mechanisms of action involved as well as technological developments and the publication of relevant studies and research related to the advantages obtained with the use photobiostimulation in clinical practice. However, the lack of consensus regarding therapeutic protocols hinders multicenter comparisons of the many clinical trials published. Thus, a number of scientific papers have been drafted to establish a therapeutic protocol for the use of photobiostimulation with regard to exposure time, intensity, energy density, application mode and application site.

A considerable number of studies have demonstrated the remission of pain in patients with fibromyalgia through the use of LLLT. However, this is not yet a well-established therapy and comparisons of controlled clinical trials are rare. Moreover, there are problems regarding the standardization of treatment [13,14,17,18]. In the investigation of complex phenomena such as fibromyalgia, the application of multiple methodological techniques enables a better assessment and understanding of such phenomena [19].

The aim of the proposed study is to assess the analgesic effect of LLLT on tender points in patients with fibromyalgia and establish correlations with quality of life and sleep.

## Methods and study design

### Characterization of proposed study

A double-blind randomized controlled trial will be carried out at the Sleep Study Laboratory of the Post Graduate Program in Rehabilitation Sciences of the Nove de Julho University (UNINOVE) and the UNINOVE Integrated Health Center, located in the city of Sao Paulo, Brazil. (Figure 1)

**Figure 1 F1:**
[figure not shown]
**Flow chart characterization of the experimental design,****sample composition and trial protocol.**

### Characterization of subjects

The sample will be comprised of 120 patients with fibromyalgia with a clinical diagnosis based on the ACR criteria. The subjects will be screened at the UNINOVE Rheumatology Clinic.

### Composition of sample

The required sample size was determined for the primary outcome variable, that is, overall score of the Fibromyalgia Impact Questionnaire (FIQ). According to Bennett *et al*. [20], a clinically relevant change is a 15 to 20% reduction in the total FIQ score (which is equal to an approximate 10 to 15 points reduction). Assuming a unilateral alternative (that is, the intervention reduces the impact of fibromyalgia), we can detect differences of at least 15% with a power of 95% and α of 0.05 with two groups (intervention and usual control group) of 45 participants, with a mean in the FIQ of approximately 70 and a standard deviation of approximately 20 points. Assuming a maximum loss of follow-up of 30%, we will recruit a total of 60 women with fibromyalgia for each group. We will recruit a total of 120 women with fibromyalgia (that is, one LLLT intervention group and control group of 60 persons each).

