### Low-level laser therapy

#### Specifications

The Twin Laser (MM Optics Ltda., São Carlos, São Paulo, Brazil) will be employed, the active medium of which is made up of a Gallium-Aluminum-Arsenide semiconductor diode, with emission in the 780 nm near infrared wavelength (invisible) and variable power values in the continuous emission mode. The display provides the doses according to the power and application time. The laser will undergo verification of functioning, energy source, points of application and measurement of power.

To provide the ‘blinding’ of the study, the laser equipment has two identical application points furnished by the manufacturer - one active and the other a placebo (that does not emit energy); both have a sound device and guide light. The points will be named A and B by a researcher who will not participate in the treatment or evaluations. The researcher performing the applications and the evaluators will be unaware of which points received the effective dose and which received the placebo. The patients will also not have access to information regarding to which group they belong. The points will be identified only at the end of the data acquisition phase.

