### Evaluation of results

The intention-to-treat analysis will be followed. The patients will be evaluated with regard to the primary outcome (pain) using the visual analog scale for pain, the McGill Pain Questionnaire and pressure algometry. The secondary outcome (quality of life) will be assessed using the SF-36 and FIQ. The use of medication will be controlled throughout the study. The data on the use of analgesics and daily dosage of adjuvant therapy, such as antidepressants and muscle relaxers, will be recorded and tabulated.

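### The protocol names two different primary outcomes, and its only sample-size calculation is for the one that it elsewhere ranks as secondary

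*Protocol article*

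**What the plan says.** Three places in the protocol article rank the outcomes, and they do not agree.

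- **Composition of sample:** "The required sample size was determined for the primary outcome variable, that is, overall score of the Fibromyalgia Impact Questionnaire (FIQ"). The calculation takes a difference of at least 15%, a mean of about 70, an SD of about 20, 95% power and α of 0.05. It is one-sided: "Assuming a unilateral alternative (that is, the intervention reduces the impact of fibromyalgia"). It arrives at 45 per group, raised to 60 for loss to follow-up.
- **Abstract, Methods/design:** "The patients will be evaluated regarding the primary outcome (pain) using the following instruments: visual analog scale, McGill Pain Questionnaire and pressure algometry". The FIQ is in the next rank: "The secondary outcome (quality of life and sleep) will be assessed with the following instruments: Medical Outcomes Study 36-item Short-Form Health Survey, Fibromyalgia Impact Questionnaire".
- **Evaluation of results:** "The patients will be evaluated with regard to the primary outcome (pain) using the visual analog scale for pain", followed by the McGill questionnaire and algometry. Then: "The secondary outcome (quality of life) will be assessed using the SF-36 and FIQ".

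The Background states the purpose in terms of pain: "The aim of the proposed study is to assess the analgesic effect of LLLT on tender points in patients with fibromyalgia". The Statistical analysis section sets one 5% level. It does not say whether tests are one- or two-sided, and it does not divide the level among outcomes. No pain instrument is given a target difference or an SD anywhere.

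**The concern.** The FIQ total score cannot be both the primary outcome variable and a secondary outcome. An analysis plan could follow only one of the two statements, so the other has to be corrected. This is a contradiction in the current text, not a detail left to a fuller document.

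Two things are at stake. First, if the FIQ and pain give different answers, the article can be cited for a positive or a negative trial. Because pain itself has three instruments and no lead, four measures can claim to be decisive. Second, the power statement belongs to the FIQ. A reader who takes pain as primary has no stated power for it at all.

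**Working it through.** **1. The rankings side by side**

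| Section | FIQ total | Pain (VAS, McGill, algometry) |
|---|---|---|
| Composition of sample | primary, sized | not mentioned |
| Abstract, Methods/design | secondary | primary, not sized |
| Evaluation of results | secondary | primary, not sized |

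**2. The plan's own figure**

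Inputs from Composition of sample: difference 15% × 70 = 10.5 points, SD 20, one-sided α 0.05, power 95%. The normal-approximation formula for two means is

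n per group = 2 × (SD/difference)² × (z_α + z_power)², with z_α + z_power = 1.645 + 1.645 = 3.290.

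- 10.5 points: 2 × (20/10.5)² × 3.290² = 78.5, so 79 per group. The stated 45 is not reproduced.
- 14 points (20% of 70): 2 × (20/14)² × 3.290² = 44.2, so 45 per group. This matches the stated number.
- Power for 10.5 points with 45 per group: 80.1% one-sided (79.6% by noncentral t) and 70.2% two-sided (69.3% by noncentral t).

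So 45 per group goes with the upper end (20%) of the article's 15 to 20% range for a relevant change, not with the 15% that the calculation names.

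**3. What 45 per arm can detect on a pain measure**

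No difference or SD is given for pain, so only the standardised effect can be computed: d = (z_α + z_power) × √(2/45), where √(2/45) = 0.2108.

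- 95% power, one-sided 5% (the plan's settings): 3.290 × 0.2108 = 0.69 SD.
- 95% power, two-sided 5%: (1.960 + 1.645) × 0.2108 = 0.76 SD.
- 80% power, two-sided 5%: (1.960 + 0.842) × 0.2108 = 0.59 SD, or 0.60 by noncentral t.

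The 80% line is a common reference, not a figure from the article.

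**4. Four candidate measures, each tested at 5%**

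The candidates are the FIQ, VAS, McGill and algometry. Two-sided tests are assumed.

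- Independent: 1 − 0.95⁴ = 18.5% chance of at least one significant result in either direction under no effect.
- Common correlation of 0.5 (assumed, since the article gives none): about 15.6%, by numerical integration of the equicorrelated normal distribution.
- In favour of the laser only, independent: 1 − 0.975⁴ = 9.6%.

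**The case against.** The strongest reply is that the intent is plain. The aim, the abstract and Evaluation of results all put pain first, and only the sample-size section differs. Sizing a trial on a secondary measure is also legitimate when it is declared. The first part stands: a reader might infer that the trial's question is wholly open, and the text does not support that, because it leans towards pain. The second part does not help, because the sample-size section does not declare a secondary outcome. It calls the FIQ primary.

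A second reply is that the error rate overstates the danger. This stands in part. The 18.5% counts false results in either direction, is the independent case, and assumes that any of the four measures could be reported as decisive. It is a ceiling for that situation, not the chance of a false claim for the laser.

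A third concerns step 2: a baseline-adjusted or change-score analysis could have more power than a comparison of end values with SD 20. With an assumed baseline correlation of 0.7, the SD of change is 20 × √(2 × 0.3) = 15.5, and 45 per group gives 94% power one-sided for 10.5 points. At a correlation of 0.5 the change score gains nothing and power stays at 80%. The article states no correlation, so its 95% cannot be credited on this ground.

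Two further inferences are tempting and should not be drawn. One is that the laser key, opened when data collection ends ("The points will be identified only at the end of the data acquisition phase"), lets the outcome be chosen with the allocation known. Opening the key then is ordinary. A difference between A and B is also visible without the key, so its timing does not cause the problem. The other is that VAS is the intended lead measure. The article does not say so, and the aim's reference to tender points suits algometry at least as well.

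**Conclusion.** The contradiction holds and needs correction. The FIQ is called primary in the section that sizes the trial and secondary in the two sections that list the outcomes, and no pain measure is sized. The stated 95% power therefore does not apply to the outcome that the abstract and Evaluation of results call primary. It does not hold for the FIQ at a 15% difference either: with SD 20 applied to the compared scores, power is about 80% one-sided and 70% two-sided.

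Leaving four measures eligible at 5% each gives up to 18.5% for at least one false-positive result in either direction, or about 15.6% at an assumed correlation of 0.5. The contradiction itself rests on the text alone and needs none of these figures.

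**What to change.** Before the A/B key is opened, name one primary outcome with one instrument at the end-of-program evaluation. Use it identically in the abstract, Composition of sample and Evaluation of results, and make the other measures secondary. The aim and the two outcome sections favour pain, but the sponsor must choose the instrument, VAS or algometry.

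- **If pain is chosen:** relabel the FIQ as secondary in Composition of sample, keep 60 per arm, and state the detectable difference for the chosen instrument. With 45 per arm this is about 0.69 SD (95% power, one-sided), 0.76 SD (95%, two-sided) or 0.60 SD (80%, two-sided). Convert it to the instrument's units with an SD that the sponsor can justify.
- **If the FIQ is chosen:** change the abstract and Evaluation of results. Also restate the power as about 80% one-sided (70% two-sided) for 10.5 points, SD 20 and 45 per group, or say that 95% one-sided power applies to 14 points (20%).

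In either case, state whether the primary test is one- or two-sided.

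The cost is protocol wording, and the article reports that recruitment was still under way. No extra patients or visits are needed, with one exception: keeping 95% one-sided power for a 10.5-point FIQ difference would take 79 analysed per group unless a more efficient analysis is specified and justified.

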### Statistical analysis

ANOVA test with repeated measurements for the time factor will be performed to test between-groups differences (followed by the Tukey-Kramer post hoc test), and a paired *t* test will be performed to test within-group differences. The level of significance for the statistical analysis will be set at 5% (*P* ≤0.05).

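### The sample-size paragraph claims 95% power for a 15% FIQ difference with 45 per group, but its own inputs give about 80%; either the 15% or the 95% is wrong

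*Protocol article*

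**What the plan says.** The Composition of sample section of the protocol article bases the sample size on the FIQ total score. It sets the scale of a worthwhile effect: "a clinically relevant change is a 15 to 20% reduction in the total FIQ score (which is equal to an approximate 10 to 15 points" of reduction. It then makes the power claim: "we can detect differences of at least 15% with a power of 95% and α of 0.05 with two groups", each of 45 participants, "with a mean in the FIQ of approximately 70 and a standard deviation of approximately 20 points". The test is directional: "Assuming a unilateral alternative (that is, the intervention reduces the impact of fibromyalgia"). Allowing for a loss to follow-up of up to 30%, the section recruits 60 per group, 120 in all.

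The Statistical analysis section plans the comparison as follows: "ANOVA test with repeated measurements for the time factor will be performed to test between-groups differences". Tukey-Kramer post hoc testing follows, at a 5% significance level. It does not mention a one-sided test.

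The article gives no correlation between baseline and follow-up FIQ scores, and the sample-size paragraph mentions no baseline adjustment.

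**The concern.** The paragraph prints every input needed for a two-group power calculation, so the stated power can be checked directly. A difference of about half an SD with 45 per group does not normally give 95% power.

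This matters because 15% is the smallest FIQ change that the section calls clinically relevant. Someone reading a null FIQ result against the stated design would suppose that a true effect of that size had only a 5% chance of being missed. If power is about 80%, that chance is about 20%, four times as large. This paragraph is also the only justification the article gives for recruiting 120 patients.

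**Working it through.** **Inputs, all from Composition of sample:** mean FIQ 70; SD 20; smallest difference 15%; n = 45 per group, equal allocation; one-sided alpha 0.05; stated power 95%; loss up to 30%; 60 recruited per group.

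**Formula.** For two independent means, the standard error is SD × √(2/n) = 20 × √(2/45) = 4.216. With difference Δ, the normal approximation to power is Φ(Δ/4.216 − z), where z = 1.645 one-sided or 1.960 two-sided. (The far tail of the two-sided test is negligible here.) The exact version uses the noncentral t with 2 × 45 − 2 = 88 degrees of freedom.

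**Trying to reproduce the stated 95%.**

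- At the stated 15%: Δ = 0.15 × 70 = 10.5, standardised 10.5/20 = 0.525. Then 10.5/4.216 = 2.490, and 2.490 − 1.645 = 0.845. Power is 80.1% (normal) or 79.6% (t). The stated 95% is not reproduced.
- At 20%: Δ = 0.20 × 70 = 14, standardised 0.70. Then 14/4.216 = 3.320, and 3.320 − 1.645 = 1.675. Power is 95.3% (normal) or 95.1% (t), and 45 is exactly the n required for 95%. The stated pair of 45 and 95% is reproduced here.
- Smallest Δ with 95% power at n = 45: (1.645 + 1.645) × 4.216 = 13.9 points, and 13.9/70 = 19.8%.
- SD that would give 95% at 10.5 points: 10.5/[(1.645 + 1.645) × √(2/45)] = 15.1, against the stated 20.
- n that would give 95% at 10.5 points: 80 evaluable per group one-sided, 96 two-sided (noncentral t).

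**Direction of the test.** The ANOVA F test and Tukey-Kramer comparisons have no direction. Treated as a simple two-sided comparison of two means with SD 20, the power at 10.5 points is Φ(2.490 − 1.960) = Φ(0.530) = 70.2% (normal) or 69.3% (t). At 14 points it is Φ(3.320 − 1.960) = Φ(1.360) = 91.3% (normal) or 90.7% (t).

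**What repeated measures would do.** Power of a group-by-time test depends on the baseline-to-follow-up correlation r, which the article does not give. Assume SD 20 at both visits. The change score then has SD 20 × √(2(1 − r)). At 10.5 points with 45 per group (noncentral t):

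| Assumed r | One-sided | Two-sided |
|---|---|---|
| 0.3 | 67% | 55% |
| 0.5 | 80% | 69% |
| 0.7 | 94% | 89% |
| 0.8 | 99% | 97% |

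**Numbers actually left after loss.** 60 × (1 − 0.30) = 42, not 45. Keeping 45 after a 30% loss needs 45/0.70 = 64.3, so 65 recruited. A loss of 25% is what leaves 45 of 60 (45/60 = 0.75). Power by noncentral t, SD 20:

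| Evaluable per group | 10.5 points, one-sided | 10.5 points, two-sided | 14 points, one-sided | 14 points, two-sided |
|---|---|---|---|---|
| 42 | 77% | 66% | 94% | 89% |
| 45 | 80% | 69% | 95% | 91% |
| 60 (no loss) | 89% | 81% | 98% | 97% |

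Even with no loss at all, 15% is not detected with 95% power on the stated inputs.

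**The case against.** The arithmetic at 10.5 points is not open to dispute, and no other section corrects it. The objections concern how far one may go beyond it.

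*The inputs are approximate.* This does not close the gap. The SD would have to be about 15 rather than about 20, or the difference about 14 points rather than 10.5.

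*The planned analysis uses repeated measures, which can raise power.* This stands as a limit on the two-sided figure. A reader might infer that 69% is the power of the analysis the trial will run. The article does not support that: 69% belongs to a two-sided comparison of single measurements with SD 20, or to a change score if r happens to be 0.5. Over assumed correlations from 0.3 to 0.8, change-score power runs from about 55% to 97%. Nor does this rescue the 95%. Even a one-sided change-score test needs a correlation a little above 0.7, and the sample-size paragraph neither states nor uses one.

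*How the error arose.* A reader might infer that n was computed at the upper end of the 15 to 20% range and the lower end was then reported. The exact match at 14 points makes this plausible, but the article does not say so. A slip of 15% for 15 points would give 97% one-sided or 94% two-sided, also close to the stated figure. On either reading the power is what was intended and the effect is misprinted, so the sponsor has to say which figure is wrong.

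*The FIQ may not be the primary outcome.* Composition of sample calls it primary, but the Abstract and Evaluation of results make pain primary, and Evaluation of results lists the FIQ as secondary. So one cannot infer that the trial's main conclusion rests on this power figure. That contradiction needs its own resolution. It does not make the printed power correct.

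*Sidedness is a design choice.* That is true, and the Statistical analysis section never states sidedness. What stands is only that a directional calculation is paired with procedures that have no direction.

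**Conclusion.** The power statement is wrong as written. On the section's own mean, SD, group size and one-sided alpha, power for a 15% difference is about 80%, some 15 percentage points below the stated 95%. The risk of missing that difference is about 20%, not 5%. The stated 95% holds with 45 per group only for about 14 points, or 20%. This rests on a plain comparison of two means with SD 20, which is the only calculation the printed inputs support.

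A second, conditional point is that the one-sided calculation does not match a non-directional analysis. Two-sided power at 10.5 points is about 69% under the same plain comparison. It could be lower or higher under a change-score analysis, depending on a correlation the article does not give.

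A smaller inconsistency in the same paragraph is that the stated loss leaves 42 per group, where power at 10.5 points is 77% one-sided and 66% two-sided.

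**What to change.** This is a correction to the text, with no additional enrolment.

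1. The sponsor should confirm whether the 15% or the 95% was the intended figure, and restate the paragraph accordingly. Suggested wording: 'Assuming an FIQ SD of 20 and a one-sided 5% test, 45 evaluable participants per group give about 80% power for a 15% (10.5-point) difference and 95% power for a 20% (14-point) difference.'
2. Make the sidedness of the calculation and of the planned test agree. If the test is to be two-sided, the equivalents are about 69% and 91%. If the calculation is to take credit for repeated measures, state the assumed baseline-to-follow-up correlation.
3. Either give the power at the 42 per group that remain after 30% loss (77% one-sided, 66% two-sided at 10.5 points) or correct the stated loss. A 25% loss is what leaves 45 of 60.

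The cost is one paragraph of protocol text and a less favourable stated power.

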#### Educative session

The educative session will be individual and carried out following the initial evaluation. The subject will be informed with regard to the nature of fibromyalgia, symptoms, treatment (stressing the importance of exercise) and consequences for activities of daily living. Some exercise strategies will be taught, such as extra body weight loading and adequate positions for the performance of activities of daily living and practice (work). A basic exercise program will then be taught, composed of 11 exercises for stretching the gluteus, paravertebral, hamstrings, pectoral, scalene, intercostals and trapezius muscles. The patients will receive a chart with all the information on fibromyalgia as well as illustrations and descriptions of the exercises to perform. The chart will be furnished to all patients in order to increase compliance with the at-home exercise program.

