### Exercises

Both groups (LLLT and control) will undergo a 50-mintue exercise program following the application of the laser or placebo, which will consist of 10 minutes of warm up and stretching, 30 minutes of aerobic exercise on a treadmill and 10 minutes of relaxation and stretching, three times a week throughout the four weeks of the study.

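### The sample-size paragraph mislabels the control arm and does not say that its 15% FIQ difference is net of control-arm change; for that net difference, 45 per group gives about 80% power, not 95%

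*Protocol article*

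**What the plan says.** The Composition of sample section starts from a published threshold: "a clinically relevant change is a 15 to 20% reduction in the total FIQ score". It adds that this is roughly 10 to 15 points. It then assumes a one-sided alternative and makes its power claim: "we can detect differences of at least 15% with a power of 95% and α of 0.05". The comparison behind that claim is described as one "with two groups (intervention and usual control group) of 45 participants". The FIQ is taken to average about 70 points, with an SD of about 20. On attrition it says: "Assuming a maximum loss of follow-up of 30%, we will recruit a total of 60 women with fibromyalgia for each group".

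The treatment sections describe the second arm differently from that label:

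- **Specifications and Application of laser:** both arms have twelve sessions with identical-looking applicators, one of which emits no energy.
- **Educative session:** every patient is taught about the condition and shown a home programme. "The chart will be furnished to all patients in order to increase compliance with the at-home exercise program".
- **Exercises:** "Both groups (LLLT and control) will undergo a 50-mintue exercise program following the application of the laser or placebo", three times a week for four weeks. Under Blinding procedures, a trained examiner conducts these sessions.

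By design, the only difference between the arms is the emitted energy.

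**The concern.** Two things in the sample-size paragraph do not fit the rest of the article.

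First, the word *usual* does not describe a control arm that gets sham laser, education and twelve conducted exercise sessions. The Background itself lists exercise among the treatments for fibromyalgia, so some improvement in this arm is plausible.

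Second, the threshold is introduced as a reduction in FIQ, and the next sentence uses the same percentage as a difference between two groups. The two are equal only if controls do not change, or if the target is declared to be net of their change. The paragraph says neither.

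What is at stake is how the trial's sensitivity is understood. A reader told that power is 95% for a 15% effect will take a null FIQ result as strong evidence against laser. If the power for a net 15% difference is nearer 80%, and lower for anything smaller, that reading is too confident.

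**Working it through.** **Inputs, all from Composition of sample:** mean FIQ about 70; SD about 20; target 15%, so 0.15 × 70 = 10.5 points; one-sided alpha 0.05; stated power 95%; 45 analysed per group; 60 recruited per group; loss up to 30%.

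**Step 1. Try to reproduce the stated n.** For two equal groups,

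n per group = 2 × [(z₁₋α + z_power) × SD / difference]²

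- 10.5 points, 95% power: 2 × [(1.645 + 1.645) × 20 / 10.5]² = 78.5, so **79** per group, not 45.
- 14 points (20% of 70), 95% power: 2 × [(1.645 + 1.645) × 20 / 14]² = 44.2, so **45** per group.
- 10.5 points, 80% power: 2 × [(1.645 + 0.842) × 20 / 10.5]² = 44.9, so **45** per group.

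The 45 therefore matches either 20% at 95% power or 15% at 80% power. It does not match 15% at 95%. No term in the formula depends on what the control arm receives.

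**Step 2. Power that n delivers for a net between-group difference.** Two-sample t-test, SD 20, alpha 0.05:

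| Net difference | n per group | One-sided | Two-sided |
|---|---|---|---|
| 14 points (20%) | 45 | 95% | 91% |
| 10.5 points (15%) | 45 | 80% | 69% |
| 10.5 points (15%) | 42 | 77% | 66% |
| 7 points (10%) | 45 | 50% | 38% |

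The 42 is 60 × (1 − 0.30). Keeping 45 after 30% loss would need 45 / 0.70 = 64.3, so 65 recruited per group. The normal approximation gives values within about one percentage point of these (80.1% and 70.2% for 10.5 points at 45 per group).

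**Step 3. Why the definition of the target matters.** If 10.5 points is the net difference, the 10.5-point rows apply whatever the comparator. If it is instead the laser arm's own fall from baseline, the control arm's fall must be subtracted. The documents give no expected control-arm fall. As an illustration, a 5% fall (3.5 points) leaves 10.5 − 3.5 = 7 points, which is the last row. This is an assumed value, not an estimate.

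**The case against.** A reader might infer that the trial was sized for laser plus exercise against usual care, a comparison it does not make. The documents do not support that. The paragraph never says usual care, and it ends by calling the second arm simply the control group. The other sections describe a single control arm consistently. The 15% comes from a clinically relevant threshold, not from an effect seen against usual care, and it is already worded as a difference between two groups. If a net 10.5 points was meant, the required n is the same against any comparator. The Discussion also already speaks of laser in addition to exercise. All of this stands, and it limits the comparator point to a mislabel and an undefined target.

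The power at 7 points rests on an assumed control-arm fall. It shows only that a smaller true difference has less power, which holds for any trial. This also stands, so that figure belongs in the plan only as a labelled sensitivity value.

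A third objection is that the Statistical analysis section plans a repeated-measures ANOVA, which could be more efficient than a comparison of single post-treatment scores. It could, but that depends on a baseline-to-follow-up correlation the article does not give. For 10.5 points at one-sided 95% power, an analysis of change needs 110, 79 or 48 per group at assumed correlations of 0.3, 0.5 or 0.7. Baseline-adjusted analysis needs 72, 59 or 41. The paragraph invokes no such correlation, so its 95% cannot be credited to one.

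Finally, the Evaluation of results section makes pain primary and FIQ secondary, while Composition of sample calls FIQ primary. That conflict needs its own resolution. It limits how far this calculation governs a null result on pain, but it does not make the stated FIQ power correct.

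**Conclusion.** The point holds in limited form. The comparator label in the sample-size paragraph contradicts the treatment sections, and the paragraph does not say that its 15% is net of control-arm change. It is not shown that n was calculated for another comparison.

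The measurable error is the power. On the paragraph's own inputs, 45 per group gives about 80% one-sided (69% two-sided) for a net 15% difference, some 15 percentage points below the stated 95% on the one-sided basis. If 30% are lost from 60, the figure is about 77% (66%). Power of 95% is reached only at about 14 points, or 20%.

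These figures assume a comparison of two means with SD 20 and no gain from baseline correlation. The shortfall at 10.5 points does not depend on any assumption about control-arm improvement; the 7-point figure does.

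**What to change.** Revise the Composition of sample paragraph and keep n:

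1. Replace the comparator label with placebo laser plus the same exercise and education programme.
2. State that the target is the between-group difference in FIQ over and above any change in the control arm.
3. Replace the 95% with about 80% one-sided (69% two-sided) for 10.5 points at 45 per group. Also give about 77% (66%) at the 42 per group left after 30% loss from 60.
4. Add one sensitivity value at a smaller net difference, for example 7 points at 45 per group: 50% one-sided, 38% two-sided. Label it as an assumption, because no control-arm improvement is given.

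The cost is a few sentences and a less favourable stated power. Recruitment, procedures and treatment do not change.
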